### Study population

Ninety-four children with CP will be included. The inclusion criteria are:

- Children with diagnosis of CP [28];

- Children classified in Levels I-IV at the Gross Motor Function Classification System (GMFCS; [29,30]);

- Children enrolled in pediatric rehabilitation care, with at least physical or occupational therapy;

- Children receiving therapy with a frequency of at least three sessions per month;

- Children aged 24 months to 47 months (2-3 years) at the time of recruitment.

The exclusion criteria are:

- Children with planned surgery or medical changes during the study that may affect their motor function;

- Children whose families feel uncomfortable or unable to respond to interviews and questionnaires in Dutch (the language of all the study materials);

- Since this an efficacy study, parents who state that they will not be able to adhere to one or two of the intervention approaches or to the treatment schedule, will not be entered in the study.

Children and their parents will be approached by their treating pediatric physician. They will receive an information letter, an informed consent form, a brochure about the LEARN 2 MOVE 2-3 study, and a brochure about participating in scientific research. The researcher will contact the parents after two weeks to respond to possible queries and provide additional information when necessary. Children of parents who give informed consent will participate in the study.

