### Sample size

Sample size was calculated for the Pediatric Evaluation of Disability Inventory (PEDI) (based on data from an earlier study [31]; with a subgroup analysis of children of 2-3 years) using the following assumptions in a one-way analysis of variance power analysis (based on a power of 80% and a two-sided α-value of 0.05). An estimated difference in the change scores between the context-focused intervention approach group and the regular care intervention group of 4.5 points (SD = 6.0) on the PEDI. Sigma for the three groups = 2.1. Taking into account the clustered nature of the sample of participating children a correction will be used, based on an average cluster size (number of children per therapist) of 2, and an ICC of 0.1. These specifications lead to a required total sample size of 85. Expecting a 10% drop-out in total 94 children will be recruited for the present study.

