#### Other study parameters

Based on the literature, it is assumed that some child- and family variables might be important in explaining effects in different groups. Therefore, the following variables will be registered systematically, and will be analyzed as potential determinants:

The gross motor ability level of the child will be classified by the *GMFCS *[29,30]. The GMFCS is a classification system based on the self-initiated movements of the child. The system consists of a 5-level ordinal scale, which describes differences in severity of mobility abilities. Level I represents the best gross motor function, level V the least. The GMFCS shows good psychometric properties [29,30].

Manual skills will be classified by the *Manual Ability Classification System (MACS*; [60]). The classification system consists of five levels, from level I 'Handles objects easily and successfully' to level V 'Does not handle objects and has severely limited ability to perform even simple actions'. The MACS has shown good reliability in children 2-5 years of age [61]. Validity of the MACS was shown in children 4-18 years of age [60]. The validity in children 2-5 years of age has not been studied yet.

Type of CP will be classified according to *Surveillance of Cerebral Palsy in Europe (SCPE) - guideline *[62]. This guideline classifies CP in the subtypes of spastic, dyskinetic, or ataxic. Also the topographical distribution is classified in children with spastic CP; unilateral involvement (hemiplegia) versus bilateral involvement (diplegia, tetraplegia).

Cognitive functioning of the child will be measured by the *Bayley Scales of Infant Development-Second edition (BSID-II) - Mental Scale*, with good psychometric properties [63].

Coping style of the parents will be measured by the *Utrechtse Copinglijst (UCL)*, a Dutch 47-item questionnaire to determine how parents handle problems and events in daily life, with sufficient psychometric properties [64].

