### Data analysis

Descriptive statistics including frequencies, means, standard deviations, and for nonparametric data medians and interquartile ranges will be calculated. Data will be analyzed based on an intention to treat-analysis. The effects of the three interventions will be evaluated using repeated-measures analysis of variance (group[3] × time[2]) with the outcome measures as the dependent variable. In case of a statistically significant interaction group × time effect, post-hoc analyses will be performed to determine between which groups the differences occur. To assess the effects during and after the six month study-intervention period, repeated-measures analysis of variance (group[3] × time[3]) with repeated contrasts will be used, with the same outcome measures.

To explore variables that might be related to the efficacy of the intervention, and that might explain possible variability between children, multiple regression analyses will be performed. The change scores on the PEDI-FSS will be the dependent variable, and the classification of gross motor abilities, classification of manual abilities, cognition of the child and coping style of the parents will be analyzed as independent variables.

The interviews with the parents on their experiences with the interventions, and therapists' preferences for intervention will be analyzed using qualitative analyses.

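### The primary group × time ANOVA is a change-score comparison with no baseline adjustment, which gives up some precision and robustness but not validity

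*Protocol article*

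**What the plan says.** The Data analysis section of the protocol article fixes the efficacy analysis as "repeated-measures analysis of variance (group[3] × time[2" levels of time, applied to each outcome. The interaction is the decisive test: "In case of a statistically significant interaction group × time effect, post-hoc analyses will be performed". No covariate appears in this model.

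The same section adds an exploratory multiple regression of the PEDI-FSS change score and lists its predictors: "the classification of gross motor abilities, classification of manual abilities, cognition of the child and coping style of the parents will be analyzed as independent". GMFCS level therefore enters an analysis only there, and treatment group is not listed among that regression's independent variables. Baseline PEDI-FSS and age enter no model.

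The sample is broad by design. Under Study population the criteria admit "Children classified in Levels I-IV at the Gross Motor Function Classification System", at ages 24 to 47 months. Under Other study parameters the authors write that "it is assumed that some child- and family variables might be important in explaining effects in different groups".

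The Sample size section works on change scores: a difference between the context-focused group and "the regular care intervention group of 4.5 points (SD = 6.0) on the PEDI", with the calculation "based on a power of 80% and a two-sided α-value of 0.05", a standard deviation of 2.1 among the three group means, two children per therapist and an ICC of 0.1. This gives 85 children, raised to 94 for drop-out.

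**The concern.** A change score subtracts the baseline with a fixed slope of 1. Unless the baseline predicts the later score with exactly that slope, this is not the most precise use of the baseline. It also leaves a residual error whenever the arms happen to differ at T0.

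Therapists are randomised in blocks of six and children follow their therapist. No balancing on the children's severity, age or starting score is stated. At about two children per therapist, 94 children means about 47 therapists, or 15 to 16 per arm, so some chance imbalance is to be expected. The plan records the variables that could absorb it but does not use them in the treatment comparison. At stake are some power in a trial sized close to its 80% target, and an estimate that is more exposed than it need be to how the arms fall at baseline.

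**Working it through.** **1. The interaction test is a change-score test.** With two time points, the group × time F equals the one-way ANOVA F on T1 − T0. On one simulated data set (three arms of 28), both routes gave F = 7.5962.

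**2. Reproducing the plan's 85.** Inputs from the Sample size section: difference 4.5, SD 6.0, SD of group means 2.1, α 0.05, power 80%, cluster size 2, ICC 0.1.
- Group means of 0, 0 and 4.5 have SD 4.5 × √2/3 = 2.12, which matches the stated 2.1. Then f² = (2.121/6.0)² = 0.125.
- The large-sample noncentrality for 2 df, α 0.05 and 80% power is 9.635, so N = 9.635/0.125 = 77.1.
- Design effect: 1 + (2 − 1) × 0.1 = 1.1. Then 77.1 × 1.1 = 84.8, rounded up to 85. The plan's figure is reproduced, and on this route power at 85 is 80.1%.
- By noncentral F with f = 2.1/6.0 = 0.35 and 85/1.1 = 77.3 effective children, the noncentrality is 77.3 × 0.1225 = 9.47 and power is 77.5%.

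**3. Gain from baseline adjustment.** Let s be the common SD at T0 and T1 (assumed equal) and r their within-arm correlation (not given in the documents). The variance of change is 2s²(1 − r). The residual variance after adjusting for baseline is s²(1 − r²). Their ratio is (1 + r)/2.

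| Assumed r | Variance ratio | Required N, plan's formula | Power at 85, plan's formula | Power at 85, noncentral F |
|---|---|---|---|---|
| no adjustment | 1.00 | 85 | 80.1% | 77.5% |
| 0.9 | 0.95 | 81 | 82.2% | 79.7% |
| 0.8 | 0.90 | 77 | 84.3% | 81.9% |
| 0.7 | 0.85 | 73 | 86.4% | 84.2% |
| 0.5 | 0.75 | 64 | 90.5% | 88.6% |

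A simulation of 4,000 trials per setting, with 26 independent children per arm, agrees. Change-score against baseline-adjusted power was 79.3% against 80.9% (r = 0.9), 78.6% against 84.7% (r = 0.7) and 79.1% against 88.9% (r = 0.5). Both estimators averaged about 4.5, so neither is biased.

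**4. Effect of a chance baseline difference.** Given a baseline difference d between two arms, the change-score estimate is off by (1 − r) × d in size, against the arm that starts higher. With change SD 6.0, s = 6/√(2(1 − r)). With 28 per arm (85/3) and clustering ignored, the standard error of d is s × √(2/28).

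| Assumed r | s | SE of d | Shift for a 1-SE imbalance | Share of 4.5 |
|---|---|---|---|---|
| 0.9 | 13.42 | 3.59 | 0.36 | 8% |
| 0.8 | 9.49 | 2.54 | 0.51 | 11% |
| 0.7 | 7.75 | 2.07 | 0.62 | 14% |
| 0.5 | 6.00 | 1.60 | 0.80 | 18% |

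**5. GMFCS and age.** Differencing removes their effect on the starting level but not any effect on the amount gained. The documents do not quantify the latter. If these covariates explained an assumed 5% to 20% of change-score variance, noncentral-F power would be 79.7% to 86.4%.

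**The case against.** The strongest reply is that nothing here is wrong. The trial is sized on change scores with a one-way ANOVA, and the planned analysis is algebraically the same test. The estimate is unbiased under randomisation, and on the formula that reproduces 85 the plan already reaches 80.1% power. A condensed article may also leave covariates to a fuller document. The first part stands in full and limits the point to efficiency and robustness. The second stands only in part: the article does not leave the model open but names a specific one without covariates.

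The size of the gain is also open to challenge. A sample spanning GMFCS I to IV and two years of age may well have a high r, and at r = 0.9 the gain is only about 2 points of power. That stands, which is why a range is given.

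A reader might infer that chance imbalance goes wholly uncorrected. For baseline PEDI-FSS that is not so: differencing removes it with slope 1, and what remains is an over-correction of (1 − r). A reader might also infer that milder or younger children gain faster. The documents say only that some child variables, gross motor ability among them, may matter, and they do not name age in that context. Finally, the exploratory regression should not be read as covering all the candidate covariates, since it omits age and baseline PEDI-FSS.

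**Conclusion.** The point holds as one of efficiency and robustness. The stated primary model is an unadjusted comparison of change, and it sets aside baseline information that the trial already has. The loss is 5% to 25% of error variance, or about 2 to 11 percentage points of power, for r from 0.9 to 0.5. A one-standard-error baseline imbalance moves the estimate by 0.36 to 0.80 points. These figures rest on an assumed r, on equal variances at T0 and T1, and on the plan's own SD and design effect. Imbalance in GMFCS level or age stays uncorrected to the extent that these predict gain, by an amount the documents do not allow one to state. The documents do not support reading this as bias in the planned estimate or as a mismatch with the sample size.

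**What to change.** Make the primary analysis a model of T1 PEDI-FSS on treatment group, with baseline PEDI-FSS as a prespecified covariate together with GMFCS level and age at T0. Report adjusted between-group differences with 95% confidence intervals. Analyse each secondary outcome measured at baseline in the same way, adjusting for its own baseline value. The 85 need not change, because adjustment can be taken as a margin on it.

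The cost is a change of analysis wording and a few degrees of freedom. No new data are needed: PEDI-FSS and GMFCS level are already collected, and age is established at eligibility. How therapist clustering is modelled is a separate question and need not be settled here.

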**Methods/Design:**

A multi-centre, randomized controlled trial research design will be used. Ninety-four children with CP (Gross Motor Function Classification System (GMFCS) level I-IV; age 2 to 3 years), their parents, and service providers (physical and occupational therapists) will be included. During a period of six months children will receive child-focused, context-focused or regular care intervention. Therapists will be randomly assigned to deliver either a child-focused intervention approach, a context-focused intervention approach or regular care intervention. Children follow their therapist into the allocated intervention arm. After the six months study-intervention period, all participants return to regular care intervention. Outcomes will be evaluated at baseline, after six months and at a three months follow-up period. Primary outcome is the capability of functional skills in self-care and mobility, using the Functional Skills Scale of the Pediatric Evaluation of Disability Inventory (PEDI). Other outcomes will be quality of life and the domains of the International Classification of Functioning, Disability and Health - for Children and Youth (ICF-CY), including body function and structure, activities (gross motor capacity and performance of daily activities), social participation, environmental variables (family functioning, parental empowerment).

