After inclusion in the study a baseline measurement (T0) will take place. Children will be assessed and parents will fill out questionnaires and will be interviewed on the measures as described in the Section Study Parameters. Parents can choose whether they would like to fill out the questionnaires on a digital or a paper version. Thereafter participants will follow their therapist into one of the three intervention groups for a six months study-intervention period. After these six months the second measurement (T1) will take place, after which all participants return to regular care intervention. At a three months follow-up period the third measurement (T2) will take place. Independent assessors who are blind for intervention allocation will asses the children and their parents.

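### The three-time-point analysis names only adjacent-time contrasts, so no planned contrast directly tests or estimates the difference between arms from baseline to T2

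*Protocol article*

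**What the plan says.** The Protocol article has three measurements. The Abstract says "Outcomes will be evaluated at baseline, after six months and at a three months follow-up period". Under Study procedures, T1 closes the intervention period: "After these six months the second measurement (T1) will take place, after which all participants return to regular care intervention". Then "At a three months follow-up period the third measurement (T2) will take place".

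The Data analysis section plans two repeated-measures analyses of variance. The first is three groups by two times. The times are not named, but T0 and T1 are implied. Its follow-on rule is "In case of a statistically significant interaction group × time effect, post-hoc analyses will be performed to determine between which groups the differences occur". The second adds the third time point, with the purpose "To assess the effects during and after the six month study-intervention period", and its method is "repeated-measures analysis of variance (group[3] × time[3]) with repeated contrasts will be used". No baseline-to-T2 contrast is named. The research questions in the Background name no time point.

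**The concern.** At T2 all children have been back on regular care for three months. An obvious question for that visit is whether one arm is still ahead of another, relative to where each started. The T0-T1 contrast covers the interval that the two-time-point analysis already appears to cover. The only comparison specific to follow-up is therefore T1-T2, which asks whether the arms diverge after the study intervention ends.

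If an advantage is fully kept, T1-T2 is null by construction. The most favourable follow-up result would then appear as a non-significant contrast, with no planned estimate of the lasting difference. An advantage that builds slowly, partly by T1 and fully by T2, could be missed by both adjacent contrasts although the arms clearly differ at T2.

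**Working it through.** **Inputs from the Sample size section.** Difference in change scores 4.5 points, SD 6.0, spread of the three group means 2.1, average cluster size 2, ICC 0.1, required total 85, and "based on a power of 80% and a two-sided α-value of 0.05".

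**Assumptions not in the document.** The SDs of T1-T2 and T0-T2 change are not given. I carry over 6.0 and show 4 to 7. One arm differs and the other two are equal. Within-child errors are independent with equal variance, so every pair of times has the same change SD.

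**1. The plan's own sample size.**
- Means (0, 0, 4.5) have spread 4.5 × √2/3 = 2.12, which agrees with the stated 2.1. Effect size f = 2.12/6 = 0.354.
- The large-sample noncentrality for three groups, 5% level and 80% power is 9.635.
- N = 9.635/0.354² = 77.1. The design effect is 1 + (2 − 1) × 0.1 = 1.1, and 77.1 × 1.1 = 84.8, so 85. The stated figure is reproduced.
- The effective number is 85/1.1 = 77.3, about 26 per arm.

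**2. What repeated contrasts cover.** On (T0, T1, T2) they are [−1, 1, 0] and [0, −1, 1]. The baseline-to-T2 contrast is [−1, 0, 1]. It is the sum of the two, so it can be estimated from the same model, but it is not one of the two that are tested.

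**3. How often each test rejects.** Simulation of the three-by-three design, 26 per arm, change SD 6, 3,000 runs. Columns two and three give the differing arm's advantage in points.

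| Scenario | At T1 | At T2 | T0-T1 | T1-T2 | T0-T2 | Overall interaction |
|---|---|---|---|---|---|---|
| Fully kept | 4.5 | 4.5 | 79% | 6% | 78% | 83% |
| Half lost | 4.5 | 2.25 | 79% | 25% | 26% | 68% |
| All lost | 4.5 | 0 | 79% | 79% | 5% | 82% |
| Late gain | 2.25 | 4.5 | 25% | 27% | 79% | 69% |

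**4. Why the overall interaction cannot tell kept from lost.** Its noncentrality is n × (2/3) × SS/σ², where SS is the sum of squares of the advantage pattern about its mean over time, and σ² = 6²/2 = 18.
- Kept (0, 4.5, 4.5): deviations −3, 1.5, 1.5, so SS = 13.5.
- Lost (0, 4.5, 0): deviations −1.5, 3, −1.5, so SS = 13.5.

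Both give 26 × (2/3) × 13.5/18 = 13.0, hence the same power, about 82%. The one-point gap in the table is simulation noise.

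**5. Formula check and sensitivity to the SD.** For a single contrast the noncentrality is N × f². With N = 77.3, a three-group F test has this power:

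| Change SD | 2.25 points | 4.5 points |
|---|---|---|
| 4 | 52% | 99% |
| 5 | 35% | 92% |
| 6 | 26% | 78% |
| 7 | 20% | 64% |

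The 2.25-point column applies equally to T1-T2 detecting loss of half the effect and to T0-T2 detecting the half that remains.

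**6. Precision of a pairwise difference.** The 95% half-width is 1.96 × SD × √(2/25.8): 2.2 points at SD 4, 2.7 at SD 5, 3.3 at SD 6 and 3.8 at SD 7. A loss of 2.25 points is about as large as the half-width at SD 4 and smaller than it at every higher SD.

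**The case against.** The strongest reply is that the contrasts do what the article says they are for: T0-T1 is the effect during the intervention period and T1-T2 the effect after it. That stands, so there is no internal contradiction. It also stands that the T0-T2 point estimate is the sum of the two planned ones and that the overall interaction includes it jointly, so it would be wrong to say that T0-T2 is outside the analysis altogether. What is missing is a contrast that isolates it.

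A reader might infer that the plan will treat a non-significant T1-T2 contrast as proof that gains were kept. The document does not support this. It mentions neither retention nor maintenance and gives no rule for reading a null contrast. The figures show only that such a reading, if anyone made it, would be weak.

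A reader might also take the low power of T1-T2 against a half loss as a reason to exchange it for T0-T2. That does not follow, because T0-T2 has the same low power in that scenario. T0-T2 alone also cannot separate a kept gain from a late one, so T1-T2 is needed as well.

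Finally, this is a condensed article and a fuller plan may list more contrasts. That limits the weight of the point but does not remove it, because the article commits to a specific contrast type.

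**Conclusion.** The point holds in limited form. With the contrasts named, the three-time-point analysis gives no direct test or estimate of the difference between arms from baseline to T2, and the overall interaction does not fill the gap. The gap matters most in two situations. If a 4.5-point advantage is fully kept, power is about 78% for T0-T2 against 5-6% rejection for T1-T2. If the gain comes late, power is about 79% for T0-T2 against 25-27% for each planned contrast. If half the effect is lost, neither follow-up contrast is strong (about 26%), and only estimates with intervals would be informative.

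These figures rest on a change SD of 6 for every pair of times, equal within-child variances, one differing arm and about 77 effective children. The SD for the follow-up intervals is an assumption. The two-time-point efficacy analysis is unaffected.

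**What to change.** In the Data analysis section, keep both repeated contrasts and add the group × (T2 versus T0) contrast to the three-time-point analysis. Report the T0-T2 and T1-T2 differences between arms with 95% confidence intervals. State that follow-up is interpreted from these estimates together, and not from non-significance of T1-T2.

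Do not substitute the new contrast for T1-T2, which is the one that addresses the period after the intervention. The cost is one more contrast in a supplementary analysis. No further children, visits or data are needed.

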In addition to the questions on efficacy, the working mechanisms of the child-focused intervention approach and the context-focused intervention approach will be examined. Parental stress, empowerment and family-centeredness of care will be analyzed in the three intervention groups. Moreover, variables that might be related to the efficacy of the intervention approaches and that might explain possible variability between children will be examined. In a longitudinal study of our research group on the development and determinants of daily activities in children with CP named PERRIN (Pediatric Rehabilitation Research in the Netherlands), and from recent literature, insight has been gained in child- and family-variables that possibly explain more about the working mechanisms of the interventions. These variables are: gross motor abilities [19,20], manual abilities [21,22], cognition of the child [21,23,24], and coping style of the parents [25-27]. We will collect data on these variables to get more insight in possible variability between children. Moreover, to get more insight into the working-mechanisms of the intervention approaches, part of the parents will be interviewed on their experiences with the interventions and therapists will be asked about preferences for intervention.

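### The exploratory regression meant to find variables related to efficacy has no arm term and no arm-by-determinant term, so it can identify predictors of change but not variables on which the effect of an approach depends

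*Protocol article*

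**What the plan says.** The protocol article states the purpose of these variables in three places.

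- **Background**: "variables that might be related to the efficacy of the intervention approaches and that might explain possible variability between children will be examined".
- **Other study parameters**: the reason given for recording them is that "some child- and family variables might be important in explaining effects in different groups". Five are then described as potential determinants: GMFCS, MACS, type of CP, cognition (BSID-II) and parental coping (UCL).
- **Data analysis**: "To explore variables that might be related to the efficacy of the intervention, and that might explain possible variability between children, multiple regression analyses" are planned.

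The model is then set out: "The change scores on the PEDI-FSS will be the dependent variable, and the classification of gross motor abilities, classification of manual abilities". The list of predictors closes with "cognition of the child and coping style of the parents will be analyzed as independent variables".

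Intervention arm appears in a different analysis, the "repeated-measures analysis of variance (group[3] × time[2]) with the outcome measures as the dependent variable", and in its three-time-point extension. Neither of those contains any of the determinants.

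**The concern.** In this trial efficacy is a contrast between arms. A variable related to efficacy, or one that explains effects in different groups, is therefore a variable across whose values that contrast changes. Estimating this needs a model in which arm and determinant meet. No analysis in the article has both.

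Two errors become possible. A factor that predicts progress equally in every arm, as a severity classification plausibly might, could be read as related to efficacy. A factor that truly alters the effect of an approach could go unseen, because its influence is averaged over arms. Either would misinform the question of which children benefit from which approach.

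**Working it through.** The plan gives no figure for this analysis, so there is none to reproduce. The check compares the model with its aim and then illustrates the consequence.

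**1. Aim against model**

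| Aim | What it requires | In the listed model? |
|---|---|---|
| Explain variability between children | Determinants as predictors of change | Yes |
| Variables related to efficacy; effects in different groups | Arm and arm-by-determinant terms | No |

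**2. What the pooled slope estimates.** With equal arms and a determinant distributed alike in each arm, the slope from a model without arm is the mean of the arm-specific slopes:

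b(pooled) = (b(child-focused) + b(context-focused) + b(regular)) / 3

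Take the slope as the difference in mean change between GMFCS I-II and III-IV. The patterns below are assumed; only the 4.5-point scale is borrowed from the Sample size section.

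- Context-focused effect of 9 points in I-II and 0 in III-IV (average 4.5 with equal halves), nothing in the other arms: (0 + 9 + 0)/3 = 3.
- Purely prognostic difference of 3 points in every arm: (3 + 3 + 3)/3 = 3.
- Context-focused helps I-II by 4.5, child-focused helps III-IV by 4.5: (-4.5 + 4.5 + 0)/3 = 0.

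The first two patterns give the same coefficient but mean different things. The third is real modification with a coefficient of zero.

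**3. Simulation.** Inputs from the Sample size section: N = 85, SD 6.0 (used as residual SD), and a 4.5-point effect in one arm. Assumed: one standardised determinant, the slopes below, no clustering, 4,000 runs, tests at 0.05.

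| Truth | Determinant significant, no arm in model | 2-df arm-by-determinant test significant |
|---|---|---|
| Prognostic only: 2.5 points per SD in every arm | 93% | 4.5% |
| Modifier only: slopes 0, -3 and +3 per SD | 7% | 88% |

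The pooled model usually flags the variable that modifies nothing, and it flags the true modifier only slightly more often than chance.

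**4. Precision of the remedy.** 85/3 is about 28 children per arm. For one standardised determinant and residual SD 6.0, the standard error of a difference in slopes between two arms is about 6.0 × √(2/28) = 1.60. The 95% interval is then roughly ±1.96 × 1.60 = ±3.1 points per SD of the determinant, before any allowance for clustering. Four determinants with two arm contrasts each make at least 4 × 2 = 8 interaction terms if fitted together. GMFCS I-IV treated as categories needs (4 - 1) × (3 - 1) = 6 by itself.

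**5. Type of CP.** Other study parameters includes it among the variables to be analysed as potential determinants. The regression in Data analysis omits it, as does the list of four explanatory variables in the Background.

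**The case against.** The strongest reply has four parts.

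- **The aim has two halves, and the model serves one.** This stands. A reader might infer that the regression cannot answer its stated question at all. The documents do not support that: explaining variability between children is an explicit part of the aim, and regressing change on these variables addresses it.
- **Working mechanisms do not depend on this regression.** This stands too. A reader might infer that the working-mechanism aim fails with it. The Background also plans group comparisons of parental stress, empowerment and family-centeredness of care, together with parent interviews and therapist preferences, and the qualitative material has its own analysis.
- **The analysis is exploratory.** True. It is not among research questions i to v, no power statement rests on it, and the group-by-time comparison is untouched. This limits the severity. It does not make the model estimate the quantity named in its aim.
- **A condensed article may not list the full model, and the plural could mean one regression per arm.** This carries some weight, but the article does name the outcome and the independent variables, so the issue is a stated model that does not match a stated aim. It says nothing of fits per arm, and separate fits without a comparison of slopes between arms would not test modification either.

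It is also fair to say that the numerical patterns are constructed. They show how the model behaves and predict nothing about this trial.

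**Conclusion.** The point holds in a limited form. As specified, the regression can identify predictors of PEDI-FSS change. It cannot identify variables related to the efficacy of the approaches or explain effects in different groups, and no other quantitative analysis in the article joins arm with these determinants. The article nowhere says that a significant coefficient will be reported as a differential treatment effect. That misreading is a risk created by the wording of the aim, not a stated intention.

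The conclusion rests on taking the listed variables as the model. The percentages and point values rest on assumed slopes and equal arms. The omission of type of CP is a small, separate inconsistency.

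Severity is moderate to minor: an exploratory secondary analysis is affected, while the primary comparison and the qualitative analyses are not.

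**What to change.** In Data analysis, for each determinant in turn, add intervention arm and the arm-by-determinant interaction to the regression of PEDI-FSS change. Base any statement about efficacy on the interaction estimates with confidence intervals. State that these are exploratory and imprecise at about 28 children per arm, and that several determinants are examined. Describe the model without these terms as a model of predictors of change, and draw no conclusion about efficacy from it. If the interaction models are not wanted, the alternative is to keep the present regression under that label and drop the efficacy aim for it.

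Reconcile the determinant lists: either add type of CP to the regression or state in Other study parameters that it is descriptive only.

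The cost is a change of wording and a few more model fits. Every variable is already collected, and the sample size and primary analysis stay as they are. Nothing else in the regression, such as the use of a change score, has to change to cure this defect.
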